### *Pilot study*

We will recruit 40-50 participants to test the intervention in September 2021. Trained SEACO research staff and CHWs will be asked to record the pilot phone calls. The research team will provide feedback and evidence-informed further training to the research staff and CHWs based on the pilot calls. All pilot participants will be surveyed and the results will inform potential modifications and further training requirements for the CHWs.

## **Evaluation**

### *Outcome measurements*

Our primary measure is the difference in CBE screening uptake between women who receive the CHW-led education and navigation intervention and women from the CG who receive usual standard practice (i.e. opportunistic screening at clinics) during the pandemic. In addition to increased awareness about the CBE screening and engagement with the screening programme, secondary outcomes include positive change related to:

- BC symptom recognition
- Intention to attend CBE and mammogram screening
- Beliefs and barriers regarding BC and BC screening
- Practice of breast-self-examination (BSE)
- Mammogram screening attendance (for CBE positive women)

Outcomes related to the programme evaluation are informed by the RE-AIM framework, i.e. reach, effectiveness, adoption, implementation and maintenance [39], together with measures of acceptability, appropriateness and feasibility [40].

### ***Methods of assessment***

#### ***Participant information***

Information about gender, age, ethnicity, income, education, occupation, having somatic NCDs (e.g. diabetes and hypertension), body mass index (BMI), smoking status, cancer history, travel distance (km) to the nearest clinic and ownership of motorised vehicle will be extracted from the most recent health survey (2018) recorded in the SEACO database in order to present a profile of study participants. Participants will be asked questions about mobile phone ownership/usage and internet usage during the baseline survey.

#### ***Surveys (baseline and follow-up)***

The baseline and follow-up surveys will be completed over the phone. Trained SEACO data collectors will conduct telephone surveys with participants from the IG and CG that will take approximately 15-20 minutes. The follow-up survey will take between 20-25 min for the IG and 15-20 min for the CG. The surveys comprise a number of previously adapted and validated questionnaires. In order to ascertain changes in BC symptom recognition, we will include the validated Breast Cancer Awareness Measure for Malaysia (B-CAM-M) [41] before-and-after the intervention implementation. CBE and mammogram screening intentions at baseline will be measured by asking participants to respond to the statement 'I intend to have a Clinical Breast Examination to check for breast cancer in the near future', using a 5-point Likert scale (strongly disagree – strongly agree), providing the option 'I have not yet

thought about this'. Unless participants choose the last option, participants will also be asked at what age they are thinking of getting the CBE [42]. The same questions will be asked about participant's intention to attend mammogram screening. The follow-up survey will also include specific questions to assess participant satisfaction with the screening [43,44] as well as the acceptability and appropriateness of the intervention based on an adapted version of the validated Acceptability E-scale [45] (IG only).

### *BC screening attendance*

LPPKN nurses will be asked to record CBE attendance in a spreadsheet that will be shared with SEACO on a weekly basis. Mammogram attendance will be collected retrospectively from the LPPKN clinic.

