## **Abstract**

**Design and objective:** This randomized controlled study aims to evaluate an intervention in Malaysia that educates women about breast cancer (BC) screening and navigates them to Clinical Breast Examination (CBE) services and leads to an increase in BC screening uptake whilst taking account of the COVID-19 pandemic context.

**Study population:** Women who are aged 40-74 years, living in Segamat District, Malaysia, with a registered mobile phone number will be sampled randomly from the total population of women who participated in the South East Asian Community Observatory (SEACO) Health Survey (2018). BC patients or women experiencing BC symptoms at the time of recruitment will be excluded. Computer-generated random numbers will be used to assign women randomly to the intervention group (IG) or the comparator group (CG).

**Interventions:** The IG will receive a multi-component mHealth intervention i.e. information about BC will be provided through an educational website, and telephone calls and text messages from community health workers (CHWs) will raise BC awareness and offer to navigate women to CBE services. The usual free opportunistic screening service will be available for CG participants. It will not be possible to 'blind' participants, data collectors and CHWs.

**Outcome measures:** CBE screening uptake is the primary outcome measure and will be recorded by nurses conducting CBEs. Data collectors will use telephone interviews to assess differences in relation to awareness about BC signs/symptoms, intention to attend CBE and mammogram screening, breast self-examination practice and barriers to screening pre- and post-intervention. IG participants will provide an assessment of intervention acceptability and appropriateness.

**Analysis:** A Chi-square test will be used to compare the proportion of participants who attended CBE within 4-6 weeks after the baseline survey in the IG and CG. Multivariate regression analyses will be conducted to investigate between-group differences over time and variable influences on screening participation.

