### **Intervention**

The evidence synthesis presents a clear narrative with respect to the need to educate rural women about BC screening and the importance of early detection of cancer combined with community navigation to encourage women to attend BC screening. IG and CG participants will be interviewed as baseline and at follow-up four weeks after intervention delivery has been completed.

Women who will be randomized to the IG will receive an intervention consisting of mHealth education and community navigation. Our previous mass media campaign, the Be Cancer Alert Campaign (BCAC), improved BC symptom awareness in Malaysia [10] and the BCAC website, video and brochure will be used to educate women as part of this study. Women face numerous emotional, practical, socio-cultural and health-system related barriers, and most recently, concerns related to the COVID-19 pandemic. We will train local female community health workers (CHWs) who will offer women two-way communication to address their fears and help them navigate the breast health care

system [35]. Additionally, we will train 1-2 male CHWs to engage with a woman's husband or male relatives if a woman communicates to her female CHWs that she would benefit from such engagement. There are a number of health system-related barriers and we will use the family planning clinic ran by the Ministry of Women, Family and Community Development (LPPKN) in Segamat to refer women for free CBE screening. A one-off reimbursement for transportation fees to the clinic will be offered to participants. Due to the COVID-19 pandemic and the MCO in Malaysia, the uptake intervention will be delivered through mHealth. A multi-component mHealth intervention will be used to promote screening and will include a combination of telephone calls and text messages to communicate with, and navigate, participants.

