### *Comparator Group*

During the recruitment call, participants from the CG will be made aware that BC is the commonest cancer amongst women in Malaysia and about the importance of early detection. Women who will be randomized to the CG will not receive the intervention but may avail of 'usual' screening via their local clinic (subject to pandemic restrictions).

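### Attendance is recorded only at the LPPKN clinic to which intervention women are referred, so examinations elsewhere are missed, more heavily in the comparator group

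*Protocol*

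**What the plan says.** The Abstract states that "CBE screening uptake is the primary outcome measure and will be recorded by nurses conducting CBEs". The section BC screening attendance makes this operational: "LPPKN nurses will be asked to record CBE attendance in a spreadsheet that will be shared with SEACO on a weekly basis". No other source of CBE attendance is described.

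The two arms are pointed to different places:

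- **IG.** The Intervention section names one referral venue: "Ministry of Women, Family and Community Development (LPPKN) in Segamat to refer women for free CBE screening". The Intervention Group section and Figure 1 add that community health workers book the appointment there, and transport is reimbursed.
- **CG.** Under Comparator Group, these women "will not receive the intervention but may avail of 'usual' screening via their local clinic", subject to pandemic restrictions. Outcome measurements defines the contrast against "women from the CG who receive usual standard practice (i.e. opportunistic screening at clinics) during the pandemic".

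The telephone interviews, the obvious second source, are summarised in the Abstract as covering "awareness about BC signs/symptoms, intention to attend CBE and mammogram screening, breast self-examination practice and barriers to screening pre- and post-intervention". The Surveys section adds satisfaction with the screening, acceptability and appropriateness. Neither lists a question on having had a CBE since baseline.

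Statistical analysis plans a chi-square test of the two proportions. It reports the risk difference, odds ratio or relative risk as effect size, and aims at a number needed to treat.

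**The concern.** The stated outcome is CBE uptake. The outcome that will be recorded is CBE at the venue the intervention supplies. An IG woman who accepts the offer is seen by the recording clinic. A CG woman who is examined at her local clinic is counted as not screened. If the intervention did no more than move women from local clinics to LPPKN, the recorded data would still show a benefit.

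This affects the primary test, every planned effect measure and the number needed to treat. A statistical analysis plan cannot repair it, because it concerns data that would not be collected. The protocol acknowledges bias from unblinded data collectors (Participant randomization and recruitment) but does not mention this asymmetry.

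**Working it through.** **The plan's own figure.** Sampling size and procedure gives 932 women (466 per arm) for 80% power at the 5% level to detect a 9-point rise in CBE. It names no control rate. Taking the 36% who had received a CBE in the 2017 survey (Quantitative research), 36% versus 45%, two-sided, with pooled variance and no continuity correction:

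n = [1.96·√(2·0.405·0.595) + 0.842·√(0.36·0.64 + 0.45·0.55)]² / 0.09² ≈ 466 per arm.

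This matches the plan. If 36% was indeed the rate used, it describes CBE received from any provider with no 4-6 week limit, whereas the recorded endpoint is CBE at one clinic over about 4-6 weeks.

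**Bias in the risk difference.** Let e_C and e_I be the proportions of CG and IG women whose only CBE in the window is outside LPPKN. Then

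recorded difference = true difference + (e_C − e_I).

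IG women are steered to LPPKN, so e_I should not exceed e_C, and the bias is zero or upward.

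**Size.** The protocol gives no 4-6 week background rate, so the following are assumptions: CG uptake q, share missed m, and e_I = 0. Bias = q·m.

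| q | m = 50% | m = 100% |
|---|---|---|
| 1% | 0.5 points | 1 point |
| 2% | 1 point | 2 points |
| 5% | 2.5 points | 5 points |

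**Number needed to treat.** With a true difference of 9 points it is 1/0.09 = 11.1. At q = 5% and m = 100% the recorded difference is 14 points, giving 1/0.14 = 7.1. At m = 50% it is 11.5 points, giving 8.7.

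**Ratio measures.** These are distorted even when e_C = e_I. Take q = 5%, half of it outside LPPKN in both arms, and a true 9-point gain at LPPKN. True relative risk = 14/5 = 2.8. Recorded relative risk = 11.5/2.5 = 4.6. The risk difference is 9 points either way. If no CG event is recorded, the relative risk and odds ratio have no finite estimate.

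**False rejection with no true effect.** Assume uptake q in both arms, 466 per arm, and every IG examination at LPPKN.

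- With no CG event captured, the comparison is k/466 against 0/466. An uncorrected chi-square reaches p < 0.05 at k = 4 (p = 0.045). A continuity-corrected chi-square or Fisher's exact test needs k = 6 (p = 0.041 and 0.031).
- The rejection probability is then P(k ≥ 4) or P(k ≥ 6) for k ~ Binomial(466, q).
- With half of CG events captured, both counts are binomial, with rates q and q/2.

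| q | No CG capture, uncorrected | No CG capture, corrected or Fisher | Half captured, uncorrected |
|---|---|---|---|
| 1% | 69% | 32% | 13% |
| 2% | 98% | 90% | about 22% |

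The nominal rate is 5%. With identical any-provider ascertainment in both arms, this artefact disappears.

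**The case against.** Several stronger statements are tempting, and the documents do not support them.

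- **That the bias always favours the intervention.** IG women keep access to usual clinics, and their examinations there are missed too. If uptake outside LPPKN were equal in the two arms, the risk difference would be unbiased.
- **That CG examinations are known to occur and go unrecorded.** The 2017 survey's 74% living within 30 minutes of a clinic offering CBE shows access, not events in the window. Only 46% knew that their nearest clinic offered it, and pandemic restrictions applied. Background uptake may be very small. CG women are also not barred from LPPKN and could be counted there.
- **That the follow-up survey contains no attendance question.** The questionnaires are not reproduced, and screening history appears among the regression factors in Statistical analysis. What can be said is that no such item is stated or tied to the primary outcome.
- **That a false-positive rate of 69% or 98% is to be expected.** These figures need no CG capture, full IG capture and an uncorrected chi-square.

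It may also be argued that the Abstract speaks of nurses conducting CBEs in general. However, only LPPKN nurses are given a recording task.

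These points limit the size and certainty of the bias. They do not remove the asymmetry, for which the document offers no second source.

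**Conclusion.** The point holds. As written, the plan measures CBE at LPPKN and calls it CBE uptake, and the missed examinations should fall more heavily in CG.

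The direction follows from the design: the risk difference is biased by zero or upward, provided that IG women do not use other clinics more than CG women do. The relative risk and odds ratio are inflated whenever the intervention raises uptake and some examinations take place elsewhere.

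The size cannot be settled from the protocol. The range of 0.5 to 5 points rests on assumed CG uptake of 1-5%, 50-100% of it missed and no IG examinations elsewhere. The 69% and 98% (or 32% and 90%) rejection rates are a worst case. Even with half of CG events captured, rejection exceeds 5% under these assumptions. Because this touches the primary conclusion and can be prevented cheaply before data collection, it should be fixed.

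**What to change.** 1. Define the primary outcome as CBE at any facility within the stated window.
2. Match the LPPKN spreadsheet against the participant lists of both arms.
3. Add the same question to the follow-up call already made to IG and CG: any CBE since the baseline survey, where and when.
4. Apply any confirmation with other clinics identically in both arms.
5. Report LPPKN-recorded uptake and record-confirmed uptake beside the primary result as sensitivity analyses. Data collectors know the allocation, and encouraged IG women may over-report, so self-report should not stand alone.

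If any-facility ascertainment is not adopted, label the endpoint and the number needed to treat as CBE at LPPKN throughout.

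The cost is one survey item, a protocol amendment and modest confirmation work with local clinics. The price in data quality is some self-report error and loss to follow-up non-response. The sample size need not change on this account if 36% versus 45% is the design assumption.

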### *Statistical analysis*

Quantitative data will be analysed with SPSS vs 24. Descriptive statistics at baseline will be reported as mean (SD) for continuous data and frequencies (percentages) for categorical data. The change in screening uptake and other outcomes will be compared between the IG and CG using student independent samples t-test and Chi-square tests. A Chi-square test will compare the proportion of IG and CG participants who attended CBE after completion of intervention delivery, approximately 4-6 weeks after completing the survey. The difference in proportion or odds ratio or relative risk (and 95% CI) will be used as an initial indicator of effect size and we will aim to estimate the 'number needed to treat' in terms of the number of patients that would need to be given the intervention for one extra to be screened (via CBE). Change within groups will be analysed using paired samples t-test for continuous variables and Chi-square test for categorical variables. Multivariate regression models will be used to investigate factors (e.g. ethnicity, age, income, marital status, education, BC history and BC screening history) affecting screening participation.

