### *Sampling size and procedure*

Women from Sungai Segamat and Jabi will be randomized to either IG (n=466) or CG (n=466) prior to recruitment. A sample of 1600 women (n=800 for the IG and CG) will be drawn from the SEACO database to account for participants who are not interested in participating. A sample size of 932 will allow 80% power to detect, as statistically significant at the 5% level, an increase of 9% or more in the proportion aware of a BC symptom in the IG compared to the CG after the intervention (based upon baseline awareness of a breast lump as a cancer symptom of 65% from our previous Newton-Ungku-Omar funded study). The sample size of 932 will also allow 80% power to detect an absolute increase in the proportion of women who avail of a CBE following receipt of the intervention of the intervention of 9% compared with the comparator group. The pilot will be tested with 40-50 participants.

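### Repeated survey outcomes are compared between groups as unadjusted change; adjusting the follow-up value for the baseline already collected would be more precise at no cost in data

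*Protocol*

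**What the plan says.** The Statistical analysis section of the protocol sets the between-group comparison: "The change in screening uptake and other outcomes will be compared between the IG and CG using student independent samples t-test and Chi-square tests". Its next sentence compares the proportions attending CBE once the intervention has been delivered, by chi-square, followed by a difference in proportions, odds ratio or relative risk with a 95% CI. Regression appears there for one purpose only: "Multivariate regression models will be used to investigate factors" that influence screening participation.

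The Abstract is wider: "Multivariate regression analyses will be conducted to investigate between-group differences over time and variable influences on screening participation". It names no model, outcome or covariate.

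Baseline values exist. The Surveys section places the B-CAM-M "before-and-after the intervention implementation", and the Abstract lists among the interview measures "breast self-examination practice and barriers to screening pre- and post-intervention".

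The Sampling size section frames awareness as a comparison of the two groups after the intervention: "A sample size of 932 will allow 80% power to detect" a 9-point difference "as statistically significant at the 5% level", from a reference of 65%.

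**The concern.** Subtracting the baseline gives it a fixed weight of one. Unless the correlation between the two surveys is perfect, that weight is too large and the subtraction adds noise. Regression estimates the weight from the data and so has a smaller variance. With a correlation below 0.5, the change score is noisier even than ignoring the baseline altogether.

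What is at stake is the precision of the secondary survey results. The wording also leaves two things unclear. A chi-square has no natural form for change in a yes/no item, so the effect measure for such items is open. And screening uptake has no value at baseline within the trial from which a change could be taken.

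**Working it through.** **Inputs.** From the protocol: 466 per group, 1:1 allocation, 5% level, 80% power, 9-point difference, awareness reference 65% (Sampling size and procedure; Participant randomization and recruitment); CBE received by 36% in the earlier district survey (Quantitative research). Assumed: two-sided testing (sidedness is not stated), r between 0.3 and 0.7, equal variances at both times for the continuous case, and both surveys completed by all 466 per group.

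**Step 1: the plan's own figure.** Per group, n = [1.96√(2p̄(1−p̄)) + 0.8416√(p₁(1−p₁) + p₂(1−p₂))]² / (p₂−p₁)².
- CBE, 36% vs 45%: (1.3607 + 0.5818)² / 0.0081 = 465.8, so 466 per group and 932 in total, as stated. The 36% is inferred; the Sampling size section gives no comparator rate for CBE.
- Awareness, 65% vs 74%: (1.2762 + 0.5454)² / 0.0081 = 409.6, so 410 per group. With 466 per group, a comparison at follow-up has 84.8% power, above the stated 80%.

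**Step 2: continuous survey scores.** The variance of the group difference is (2s²/n) times a factor: 2(1−r) for change, 1 for follow-up alone, 1−r² for follow-up adjusted for baseline. Adjusted over change is (1−r²)/[2(1−r)] = (1+r)/2.

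Power is shown for 466 per group at 0.1836 SD, the effect that follow-up alone detects with 80% power (2.8016 × √(2/466) = 0.1835, taken as 0.1836).

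| r (assumed) | Change factor | Adjusted factor | Ratio | Extra participants needed by change | Power, change | Power, adjusted |
|---|---|---|---|---|---|---|
| 0.3 | 1.40 | 0.91 | 0.65 | 1/0.65 − 1 = 54% | 65.9% | 83.6% |
| 0.5 | 1.00 | 0.75 | 0.75 | 1/0.75 − 1 = 33% | 80.0% | 89.9% |
| 0.7 | 0.60 | 0.51 | 0.85 | 1/0.85 − 1 = 18% | 95.1% | 97.5% |

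**Step 3: a binary item.** Awareness was simulated with 65% at baseline in both groups and 65% vs 74% at follow-up, 4,000 runs per setting. The adjusted analysis was a linear model with robust standard errors.

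| Correlation (assumed) | t-test on change | Chi-square at follow-up | Adjusted for baseline |
|---|---|---|---|
| 0.3 | 70% | 85% | 88% |
| 0.5 | 83% | 85% | 94% |
| 0.7 | 97% | 85% | 99% |

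A check by hand at 0.3:
- Variance of change, CG: 2 × 0.2275 × 0.7 = 0.3185.
- Variance of change, IG: 0.2275 + 0.1924 − 0.6 × 0.2092 = 0.2944.
- Change: SE = √(0.6129/466) = 0.0363; 0.09/0.0363 − 1.96 = 0.52, or 70% power.
- Adjusted: SE = √(0.4199 × 0.91/466) = 0.0286; 0.09/0.0286 − 1.96 = 1.19, or 88% power.

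**Step 4: does another section cure this?** The Abstract's line could be read to include baseline adjustment, but the Statistical analysis section confines regression to predictors of participation and states the raw comparison for everything else. The two do not say the same thing.

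**The case against.** The strongest reply has four parts.

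- **The test is valid.** Under randomisation the change comparison is unbiased. This stands. A reader might infer from the unblocked randomisation that chance imbalance makes the change score misleading. With 466 per group, the standard error of the imbalance in a 50% characteristic is √(2 × 0.25/466) = 3.3 points, so the missing blocks add little. Enrolment after allocation by staff who know the group is a different matter, and baseline adjustment is not guaranteed to repair it.
- **The primary outcome is handled.** This also stands. The sentence after the quoted one already compares CBE attendance as a proportion after the intervention, with a confidence interval.
- **The figures cover one reading only.** This stands in part. If the chi-square on categorical items means follow-up proportions, as the Sampling size section suggests for awareness, the variance ratios in Step 2 do not apply. The comparison is then about 85% power against 88% to 99% with adjustment. A reader might take the 70% in Step 3 to show that the trial is underpowered for awareness. It does not: it needs both the change reading and a low correlation, and the protocol fixes neither.
- **Regression is already announced, and an analysis plan may give its details.** This softens the point without removing it, because the protocol itself states the unadjusted change test; the finding does not rest on an omission.

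It would also go too far to say that every secondary outcome is affected. Mammogram attendance is taken from clinic records and has no baseline value in the trial.

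**Conclusion.** The point holds for the survey outcomes measured at both times. The stated comparison of raw change is unbiased but less precise than baseline adjustment whenever the correlation is below 1. The direction does not depend on the assumed r; the size does. For continuous scores with equal variances, the adjusted variance is 0.65 to 0.85 of the change-score variance for r from 0.3 to 0.7. For binary items the loss depends on what the chi-square is applied to, and it is smaller if follow-up proportions are meant and the correlation is low. The primary CBE analysis is unaffected, and nothing here shows a bias or a validity error.

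**What to change.** - For each survey outcome measured at both times, make the between-group analysis a regression of the follow-up value on group and the baseline value of the same outcome: linear for scores, logistic with a standardised risk difference for binary items. Report the group effect with its 95% CI.
- Keep the raw-change tests as supporting results.
- State what the chi-square compares for categorical items.
- For screening intention, first set a coding rule for the option of not yet having thought about it, which lies outside the 5-point scale.
- Reconcile the Statistical analysis section with the Abstract, so that both name the same regression for between-group differences.
- Reword the change in screening uptake as uptake after the intervention; leave the primary chi-square as it is.

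The cost is wording only. The baseline values are already to be collected, and no further participants or data are needed.

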## Background

Breast cancer (BC) is the most common cancer in Malaysia with an age-standardized incidence rate (ASR) of 34.1/100,000 (2012-2016) [1] and an age-standardised mortality rate of 12.0/100,000 (2020) [2]. Prior to the COVID-19 pandemic, it was estimated that 1 in 10 males and 1 in 9 females will develop cancer before 75 years old [1] and that about one-third to one-half of cancer-related deaths could be avoided through early presentation, detection and appropriate treatment. BC patients were diagnosed at advanced stages (48%) [1] with a considerable variation in BC incidence and prognosis across ethnic groups and geographical areas in Malaysia. For example, although BC incidence was lowest among ethnic Malay women [1], late presentation and poorer survival was more prevalent among this ethnic group compared to others [3]. Women from rural areas also presented at later stages, i.e. the majority (60%) of BC patients from rural areas of Segamat district presented at stages III and IV [4].

According to the World Health Organization (WHO), early detection, treatment and management of BC are the three pillars of BC control [5,6]. Health promotion and early detection are key in LMICs where late-stage detection of BC is high [6]. The most common screening modalities are clinical breast examination (CBE) and mammogram. CBE is less cost-intensive than mammograms and evidence suggests that CBEs are as effective as mammograms in terms of mortality [7]. In Malaysia, opportunistic CBE and mammography are the two main methods of BC screening [8]. Consequently, BC screening uptake depends on doctors offering CBE and mammogram when women at average risk of BC attend the clinic and/or women being aware of BC and the importance of screening and early detection.

CBE uptake in Malaysia varies between the main ethnic groups (Malay, Chinese, Indian and indigenous women) and ranges from 37% among indigenous women to 66% among Chinese Malaysians [9]. A recent survey of 993 women in Selangor State showed that only 29.7% of study participants aged  $\geq 50$  years attended BC screening [10]. A quarter of the sample did not know 'how to go about BC screening', understanding about mammograms was lacking and willingness to participate in BC screening was low [10]. Negative beliefs and attitudes towards cancer and screening, lack of time and confidence to visit a doctor were also common barriers to help-seeking [10].

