### **Participant randomization and recruitment**

Women will be selected randomly from the two sub-districts using the SEACO database as the sampling frame and then randomized to the intervention group (IG) or comparator group (CG) with a 1:1 allocation prior to being contacted. Randomisation will be conducted by a SEACO statistician ([name]) using Stata module RANDOMIZE without blocks [34]. Participant enrolment will be conducted by trained SEACO data collectors. All randomly sampled women who were then randomized to the IG or CG will be invited to participate by trained data collectors over the phone. The resources for this study do not permit separation of enrollment and data collection procedures and, so, DCs will be aware which group the women are assigned to and this aspect may increase the risk of bias. Participants and intervention providers will not be blinded during the enrollment and surveys. CHWs will not collect outcome measures. Women who agree to participate will receive an explanatory statement about the study and a token of appreciation for their participation.

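### The primary CBE-uptake comparison is an unadjusted chi-square although predictors recorded before allocation are already held; adjusting for them is a cheap, modest gain in precision and robustness to imbalance

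*Protocol*

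**What the plan says.** The Outcome measurements section defines the primary outcome: "Our primary measure is the difference in CBE screening uptake between women who receive the CHW-led education and navigation intervention" and women receiving usual practice. The Statistical analysis section fixes the test: "A Chi-square test will compare the proportion of IG and CG participants who attended CBE after completion of intervention delivery", roughly 4-6 weeks after the survey. The Abstract also names a chi-square test. The effect measures are a difference in proportions, odds ratio or relative risk with a 95% CI, and a number needed to treat. No covariates are named for any of them.

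Regression appears twice. In Statistical analysis it serves to explore factors affecting screening participation; the examples listed do not include trial arm. In the Abstract it covers group differences over time and influences on participation.

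The Participant information section lists age, ethnicity, income and education among the items held, and ends the list with "travel distance (km) to the nearest clinic and ownership of motorised vehicle will be extracted from the most recent health survey (2018"). The stated purpose is to describe the participants. CBE intention is asked at the baseline interview: "CBE and mammogram screening intentions at baseline will be measured by asking participants to respond to the statement". The Background says that CBE uptake "ranges from 37% among indigenous women to 66% among Chinese Malaysians".

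Randomisation is done "using Stata module RANDOMIZE without blocks", before women are contacted. The same section says that data collectors know the arm when they enrol and interview, and that this may increase the risk of bias.

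**The concern.** When baseline variables predict a binary outcome, an adjusted risk difference usually has a smaller standard error than the crude one. It also removes the part of the difference that comes from imbalance in those variables. Here the variables are already in the database, predate allocation and cannot be influenced by it, and the protocol itself regards at least one of them (ethnicity) as related to uptake. Using them only to describe the sample forgoes the benefit without saving anything.

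Balance matters more than usual. No stratification is stated and there are no blocks, so only chance balances the predictors at allocation. Enrolment then follows allocation and is done by unblinded staff. The Sampling size and procedure section draws 800 women per arm to obtain 466, so up to (800 − 466)/800 = 42% of each allocated arm may not enter. Differential consent can therefore add to chance imbalance. The crude comparison leaves both in the headline estimate.

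**Working it through.** **1. Reproducing the sample size.** Sampling size and procedure states of the awareness outcome that "A sample size of 932 will allow 80% power to detect, as statistically significant at the 5% level", a 9-point increase from 65%, and then: "The sample size of 932 will also allow 80% power to detect an absolute increase in the proportion of women who avail of a CBE", again of 9 points. No comparator rate is given for CBE. Two-sided 5% and 1:1 allocation are assumed below.

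n per arm = [1.96·√(2p̄q̄) + 0.8416·√(p₁q₁ + p₂q₂)]² / d²

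- Awareness, 65% to 74%: 410 per arm, not 466.
- CBE, taking 36% (women who had received a CBE in the 2017 Segamat survey, Quantitative research section) to 45%: p̄ = 0.405, √(2p̄q̄) = 0.6942, √(p₁q₁ + p₂q₂) = √0.4779 = 0.6913. So n = (1.3607 + 0.5818)²/0.0081 = 465.8, that is 466.

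The stated 466 is reproduced by 36% versus 45%. That the design used this rate is an inference; the protocol does not say so.

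**2. Gain from adjustment at that rate.** If covariates explain a share R² of outcome variance, the effective size per arm is 466/(1 − R²). Power = Φ{[d·√n − 1.96·√(2p̄q̄)] / √(p₁q₁ + p₂q₂)}. The CI half-width is 1.96·√[0.4779·(1 − R²)/466].

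| R² | Effective n per arm | Power | 95% CI half-width (points) |
|---|---|---|---|
| 0 | 466 | 80.0% | 6.3 |
| 0.05 | 491 | 82.0% | 6.1 |
| 0.10 | 518 | 84.0% | 6.0 |
| 0.15 | 548 | 86.0% | 5.8 |

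A simulation (4,000 trials per setting, one normal covariate, adjusted logistic regression against the crude test) gives the same picture: 80.2% for both when the covariate has no effect, 79.2% versus 81.8% at a log odds ratio of 0.5 per SD, and 80.3% versus 86.9% at 1.0 per SD.

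**3. What R² can be anchored to.** Only ethnicity has usable figures. The Setting section gives national shares of 69.6% Malay, 22.6% Chinese and 6.8% Indian, rescaled to 0.703, 0.228 and 0.069. The Background gives 66% uptake for Chinese women and 37% for indigenous women as the ends of the range; the Malay and Indian rates must be assumed.

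- Malay and Indian both 37%: mean 0.436; between-group variance 0.228 × 0.772 × 0.29² = 0.0148; R² = 0.0148/(0.436 × 0.564) = 0.060.
- Malay 40%, Indian 45%: R² = 0.047.
- Malay 50%, Indian 50%: R² = 0.018.

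With the Malay rate near the lower end, R² is about 0.05-0.06, worth about 2 points of power; it is smaller if the Malay rate is higher. These are general uptake rates, not rates for a 4-6 week window.

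**4. If comparator uptake is lower, keeping 9 points and 466 per arm.**

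| Comparator vs intervention | Unadjusted power | Power at R² 0.10 |
|---|---|---|
| 20% vs 29% | 89.3% | 92.1% |
| 10% vs 19% | 97.5% | 98.5% |
| 5% vs 14% | 99.7% | 99.9% |

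**The case against.** The strongest reply is that nothing here is wrong. A chi-square test of two randomised proportions is valid, and its error rate already allows for chance imbalance, blocked or not. That stands: a reader might infer that the primary test is invalid, and the protocol does not support that.

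A reader might also infer that the trial has no power to spare. That depends on borrowing 36% from a survey of whether women had received a CBE. The endpoint is attendance within weeks, with the comparator on opportunistic screening under pandemic restrictions. At lower rates there is ample power for 9 points.

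A third tempting reading is that adjusting for baseline CBE intention would bring a large gain. The protocol gives no correlation between intention and attendance, so no large figure can be supported. Intention is also asked after allocation, by staff who know the arm and of women who are not blinded. If knowledge of the arm shifts the answers, adjusting the headline estimate for them could bias it. This objection is accepted in full.

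It can also be said that the crude measures are described only as initial indicators, that the Abstract mentions regression for between-group differences, and that an analysis plan not shown may add a model. But group differences over time fits the repeated survey outcomes better than a single attendance record. The protocol itself names the crude test for the primary comparison and nowhere clearly supplies an adjusted arm effect on CBE uptake.

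Finally, adjustment does not cure selection through unblinded consent. It corrects only the measured part.

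**Conclusion.** The point holds as a cheap improvement, not as an error. The primary contrast ignores predictors that predate allocation and are already held, in a design where unblocked allocation followed by unblinded enrolment makes measured imbalance worth correcting.

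The precision gain is modest: about 2 points of power from ethnicity alone under assumed group rates, and 2 to 6 points for R² between 0.05 and 0.15 if the 36% rate applies. It is zero if the covariates do not predict attendance, and negligible for a 9-point effect if short-window comparator uptake is low. In that last case the reason to adjust is balance, not power. Unmeasured selection at enrolment remains either way.

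**What to change.** In Statistical analysis, and correspondingly in the Abstract, pre-specify the primary estimate as a standardised risk difference with its 95% CI and the number needed to treat. Fit a logistic regression of CBE attendance on arm, age, ethnicity, sub-district, education and travel distance to the nearest clinic, then average the predicted risks under each arm over all participants. Keep the chi-square test and crude risk difference as the supporting unadjusted analysis.

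Add baseline CBE intention only in a sensitivity model, with the response for women who have not yet considered it kept as its own category rather than forced onto the 5-point scale.

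The cost is revised wording, one extra model and slightly more explanation in the report. No new data, staff or participants are needed, and naming the covariates now prevents their being chosen after the results are seen.
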